## Abstract

**Background:**

Current research indicates that obese individuals have cognitive deficits in executive function, leading to difficulties with planning, impulse control and decision-making. High levels of inflammation have been proposed to contribute to executive function deficits in individuals with obesity.

**Methods/design:**

One hundred and seventy-six obese participants will be randomly assigned to one of two groups: (1) behavioural weight loss alone (BWL) group = 8 sessions of individual BWL sessions plus 12 group BWL sessions or (2) Cognitive Remediation Therapy for Obesity (CRT-O) plus BWL group (CRT-O + BWL) = 8 sessions of individual CRT-O plus 12 group BWL sessions. The study is double blind – participants will only be told that two weight-loss treatments are being compared and research assistants conducting outcome assessments will not know participants’ group allocation. Blood tests will be conducted to measure inflammatory markers. Measurement points will be at baseline, post treatment and 1-year follow-up. The primary outcomes will be differences between treatment groups in percentage weight loss, executive function, binge eating and an examination of whether changes in executive function predict changes in weight and binge eating. Secondary outcome measures will examine changes on inflammation, quality of life, and grazing behaviour and whether these predict changes in executive function and weight.

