Our recent randomised controlled trial (RCT) on CRT-O for obesity [16] provided evidence for the efficacy of CRT-O. Eighty obese individuals received three 90-min sessions of behavioural weight loss (BWL: a standard weight-loss treatment) and were then randomised to either eight sessions of individual face-to-face CRT-O or a no-treatment control condition. Results showed that those in the CRT-O group experienced a significant improvement in executive function and a significant decrease in weight compared to controls, both with large effect sizes, and that changes in executive function predicted changes in weight. Participants also had a significant reduction in binge eating in the CRT-O condition, compared to controls. This highlights that CRT-O can improve executive function and help individuals to manage their weight. The data from this trial suggests that CRT-O could enhance weight-loss outcomes, without targeting eating or exercise behaviour directly.

Our present RCT will endeavour to determine the effectiveness of eight individual sessions of CRT-O plus 12 group sessions of BWL compared to eight individual and 12 group sessions of BWL alone (standard care) in obese patients, in terms of reducing weight, binge eating, grazing, and improving executive function and quality of life. In addition, as high levels of inflammation have been proposed to contribute to executive function deficits in obese individuals, inflammatory markers will be assessed to test this hypothesis [17]. We hypothesise that those who receive CRT-O plus BWL will show greater weight loss, improved executive functioning and quality of life, and reduced binge eating/grazing compared to individuals in the BWL alone condition at post-treatment and 1-year follow-ups.

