### Assessment

Participants will complete a comprehensive assessment at baseline, at post-treatment and 1-year follow-ups consisting of:
*Demographics*: age, sex, ethnicity/race, socioeconomic status (by postcode, income, education), and language use
*Anthropometric measures*: we will measure: (1) height and weight with calibrated scales (to derive BMI in kg/m^2^), (2) hip and waist circumferences to calculate the waist to hip ratio, and (3) we will use a portable bioelectrical impedance scale (from Tanita) to calculate an estimate of total body water, which can then be used to estimate fat-free body mass and, by difference with body weight, body fat. (One study showed that Tanita and DEXA measures correlated at 0.96 [24]). Weight will be measured at every session
*Exercise*: participants will wear an accelerometer for 1 week (at three time points) to assess physical activity levels. Accelerometers are effective tools that continuously record physical activity over specified time intervals. The data output also allows for an estimate of physical activity intensity and energy expenditure (which are not possible with alternative methods, such as pedometers). To not over-burden participants during assessment (week 0), the accelerometer will be provided in week 1 of the intervention
*Neuropsychological assessment*: a targeted assessment of cognitive function will be completed at the time of their preference. It will include:
*Executive function:* the *Wisconsin Card Sorting Test* (WCST)-64: the computerised version of the WCST [25, 26] will be used. In this test, subjects are instructed to categorise a series of cards according to one of three stimulus features (colour, shape or number), without this principle being revealed to the subject. After each association, the only feedback given is whether a match is correct or incorrect, the idea being that subjects should infer how to categorise based on the feedback they receive. This test measures categorisation, inference, testing of hypotheses, cognitive flexibility, cognitive inhibition and response to feedback [27]. The number of total errors and perseverative errors and failure to maintain a set are the dependent measures. The WCST is regarded as a valid measure of abstract reasoning ability to maintain and appropriate planning and problem-solving strategies across changing stimulus conditions to obtain a future goal; it is the most widely used test of executive function [28]

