*Trail Making Test* (TMT) [29]: this will be used to assess psychomotor speed, visual integration, cognitive flexibility and inhibitory control. This test measures the subject’s ability to connect written numbers in an ascending order (Trail A), and, afterwards, to connect numbers and letters, alternating numbers in ascending order and letters in alphabetical order (Trail B), for example, 1-A-2-B. The score is the response time taken to complete the respective trails [28]
*Behaviour Rating Inventory of Executive Function* (BRIEF-A): participants will complete the BRIEF-A Self-report Form. This instrument is a 75-item standardised measure that records views of an adult’s executive functions or self-regulation in a person’s everyday environment. It has been shown to be a reliable and valid measure of executive functioning in individuals across a broad age range [30]
*Memory: Wechsler Memory Scale* (WMS), *Logical Memory Subtest*: the Logical Memory Test is the most widely used measure of memory [31], and it targets auditory-linguistic memory. The task demands verbal recall of spoken story passages
*Language: Boston Naming Test* (BNT): the BNT is a 60-item confrontation naming test which is considered to be a reliable measure of word retrieval performance [32]
*Nutrition*: a comprehensive assessment, using a 1-week food diary, will be conducted by a dietitian and will be analysed using FoodWorks software. The Foodworks Professional package includes food composition tables and contains nutrient values for more than 4200 foods, beverages and supplements. FoodWorks is suitable for dietary analysis and meal planning
*Inflammatory markers*: tumor necrosis factor-α (TNFα), interleukin-6 (IL-6), inflammasome-activated IL-1β and C-reactive protein will be measured
*Clinical assessment*: a brief clinical assessment will verify comorbidities such as an eating disorder, depression or anxiety. The participant will also be asked questions related to their previous weight-loss attempts and beliefs about weight loss. The following measures will also be completed:

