### Main analyses

Analyses for the main results will be conducted by the researchers with assistance from a statistician. Data will be inspected for normality and nonparametric statistics applied where appropriate. Percentage weight loss will be computed. Scores on cognitive measures will be transformed into z-scores. Linear mixed models will be used to compare differences between treatment groups in percentage weight loss, executive function, binge eating and to examine whether change in executive function predicted changes in weight and binge eating.

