### Secondary analyses

To examine the baseline and prospective relationships between biological data and cognition/weight, linear or logistic regression analyses will be performed whilst controlling for potential confounders. The Bonferroni correction or FDR (False Discovery Rate) method will be used for multiple comparisons and post-hoc testing will be performed where appropriate. Secondary analyses for the other secondary measures will use either linear mixed models or repeated measure analysis of variance (ANOVA). We will report the main analyses in a separate publication to secondary analyses.

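### Three unranked primary outcomes, no primary visit and no lead executive-function score, while the only multiplicity rule is an open choice placed under Secondary analyses

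*Protocol article*

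**What the plan says.** The Methods/design part of the abstract lists the primary outcomes: "The primary outcomes will be differences between treatment groups in percentage weight loss, executive function, binge eating". The same sentence adds "an examination of whether changes in executive function predict changes in weight and binge eating". That makes three between-group comparisons and two prediction questions, in no order of priority.

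On timing, the abstract says "Measurement points will be at baseline, post treatment and 1-year follow-up". The hypothesis at the end of the Background expects benefit over "individuals in the BWL alone condition at post-treatment and 1-year follow-ups". Neither visit is called primary.

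On executive function, the Assessment section says of the Wisconsin Card Sorting Test (WCST): "The number of total errors and perseverative errors and failure to maintain a set are the dependent measures". For the Trail Making Test, which has parts A and B, it says: "The score is the response time taken to complete the respective trails". The BRIEF-A is listed as a third instrument, without naming an index or subscale. Main analyses adds "Scores on cognitive measures will be transformed into z-scores" and then treats executive function as one outcome in a linear mixed model. It does not say how the scores become one variable.

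Main analyses has no sentence on multiplicity. The only one is under Secondary analyses: "The Bonferroni correction or FDR (False Discovery Rate) method will be used for multiple comparisons". It follows directly on the regressions of biological data against cognition and weight. The power calculation concerns weight loss only.

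**The concern.** With several primary outcomes and no rule for combining them, the plan does not say what result would count as a positive trial. A null result on weight, together with one significant executive-function score at one visit, could be reported as a positive primary finding, and nothing in the article would contradict the authors.

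The correction sentence does not settle this. It sits in the section on secondary analyses and leaves the method open. Bonferroni limits the probability of any false positive in the family. FDR limits the expected share of false positives among the results declared significant. The choice changes what a significant result means, and as written it could be made after the p-values are known.

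The power calculation points one way and the outcome list another: the trial is sized as if weight loss decides it, but declared as if three outcomes do.

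**Working it through.** The article gives no family-wise error figure and no alpha, so there is no stated figure to reproduce. The check asks how far the error rate departs from 5% under each reading that the text allows.

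**Inputs from the article**
- Between-group primary outcomes: 3 (abstract).
- Visits after baseline: 2, neither primary (abstract; Background).
- Executive-function scores: 3 (WCST) + 2 (Trails A and B) + at least 1 (BRIEF-A) = at least 6 (Assessment).
- Scores if nothing is combined: 1 (weight) + 6 (executive function) + 1 (binge eating) = 8.
- Two-tailed testing (Power calculations).

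**Assumptions not in the article**
- Alpha is 0.05, two-sided.
- Any one significant result counts as success.
- Where two visits are counted, each is tested separately.
- Correlation between test statistics is 0 to 0.7 across outcomes and 0 to 0.8 across visits.

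**Independent tests:** family-wise error = 1 - 0.95^k.
- k = 3 (three outcomes, one visit): 1 - 0.8574 = 14.3%.
- k = 6 (3 x 2 visits): 1 - 0.7351 = 26.5%.
- k = 16 (8 scores x 2 visits): 1 - 0.4401 = 56.0%.

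**Correlated tests:** normal test statistics were simulated over the correlation grid above, 200,000 draws per setting. Results in favour of CRT-O means a z statistic above 1.96 in that direction only, for which the nominal rate of a single test is 2.5%.

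| Reading | Tests | Either direction | Favouring CRT-O only |
|---|---|---|---|
| Three outcomes, one visit | 3 | 11-14% | 5-7% |
| Three outcomes, two visits tested separately | 6 | 16-26% | 8-14% |
| Eight separate scores, two visits tested separately | 16 | 28-56% | 14-33% |

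The upper ends are the uncorrelated case. They agree with the formula: for one direction, 1 - 0.975^3 = 7.3%, 1 - 0.975^6 = 14.1% and 1 - 0.975^16 = 33.3%.

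**After the fix**
- One primary outcome at one visit: 5%.
- Holm across three primaries at one visit: the smallest p-value is compared with 0.05/3 = 0.0167, the next with 0.05/2 = 0.025 and the last with 0.05. Family-wise error is at most 5%.

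**The case against.** The strongest reply is that this is a journal article, and that the testing order, the composite and the visit may be set out in a full protocol or analysis plan that is not shown. That is fair for the details of the testing procedure, and their absence alone would be no finding. But which outcomes are primary is fixed in the article, as an unranked list. The correction is also fixed there, as an open choice in the section on secondary analyses. Those are statements that can be assessed.

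A reader might infer that the trial has no error control at all. The text does not support that: a correction is promised, and its sentence is not expressly restricted to secondary outcomes. What can be said is that none is stated for the primary analyses.

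A reader might also infer that a false-positive trial is likely a quarter to a half of the time. That needs alpha of 0.05, separate tests at both visits and, for the upper part, uncombined scores, with any one result in either direction counting. The article states none of these. A mixed model could use a single group-by-time test per outcome. Conversion to z-scores is a usual step towards a composite, which is neither stated nor ruled out. The hypothesis is directional and lists its benefits jointly; if every primary had to succeed, no alpha adjustment would be needed, though power would fall. These points remove the high figures as a headline, but not the problem: even with one composite and one visit the rate is 11-14%, and the article does not say that all primaries must succeed.

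Finally, a reader might argue that low power makes most positive results false. That share depends on a prior probability that the documents do not give, and the adequacy of the sample size is a separate question. The multiplicity point does not need it.

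**Conclusion.** The point holds in limited form. The article declares three unranked between-group primaries and two prediction questions, names no primary visit, and leaves executive function as at least six scores without a lead score or composite. It states no error control for these analyses, and the one rule it gives is an open choice between methods with different aims.

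On the reading most favourable to the plan short of requiring all primaries to succeed, the family-wise error is about 11-14%, more than twice 5%. With both visits tested separately it is 16-26%. The 28-56% range applies only if each executive-function score is also tested separately at both visits. If only results favouring CRT-O count, the figures are roughly half, against a nominal 2.5%. All of them rest on an assumed two-sided alpha of 0.05, on any single significant result counting as success, and on the assumed correlations.

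**What to change.** Before any unblinded analysis, adopt one of two schemes.

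1. **Single primary.** Name percentage weight loss, the outcome used for the sample size, at one stated visit. Then test one pre-defined executive-function composite and binge eating, in fixed order or by Holm.
2. **Three primaries.** Keep all three at one stated visit and apply Holm across them.

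Under either scheme:
- Define the composite: which scores enter, how they are standardised, and how they are aligned so that all point the same way.
- Name one binge-eating measure, because the Assessment section lists both the EDE-Q self-report and the EDE binge-eating subsection.
- If the later visit is chosen, fix its date. The data collection text places it one year after treatment, but Table 1 places it at week 52, which is 32 weeks after treatment ends at week 20.
- Treat individual scores, the other visit and the two prediction analyses as supportive.
- Replace the open choice with one named correction method for the secondary analyses.

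The cost is wording in the protocol and analysis plan and a dated registry update, since recruitment has begun. Under the first scheme executive function and binge eating lose an unadjusted primary claim. Under the second the thresholds are stricter: at Holm's first step, 0.0167 in place of 0.05, the same 80% power in a simple two-group comparison needs about 1.33 times as many participants (524 against 393 per group at d = 0.2). No new data collection is needed.

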**Discussion:**

If CRT-O + BWL is more effective in assisting people to lose weight long term than BWL alone it should significantly improve treatment outcomes. This study expands upon our recent trial which showed that CRT-O enhanced executive function and weight loss in obese adults. The current study is strengthened by several factors: it is double-blind, it uses an active control, has a larger sample size, and measures inflammation to examine the mechanisms.

**Trial registration:**

The RCT is registered with the Australian New Zealand Registry of Clinical Trial, trial identifier: ACTRN12616000658415. Registered on 20 May 2016.

**Electronic supplementary material:**

The online version of this article (doi:10.1186/s13063-017-1778-x) contains supplementary material, which is available to authorized users.

## Background

According to the World Health Organisation more than 1.9 billion adults are overweight and of these 600 million are obese [1]. Between 1980 and 2014, the prevalence of obesity has more than doubled [1]. In Australia, the economic costs of obesity have been estimated at AU$21 billion a year [2]. Furthermore, the disability associated with obesity and its consequences has been calculated at over 36 million disability-adjusted life years, due mainly to ischemic heart disease and type 2 diabetes [3]. The comorbidities related to obesity, such as type 2 diabetes and coronary heart disease, however, are alleviated by modest weight loss [4] and long-term maintenance of the reduced weight [5]. Recommendations for obese individuals include losing 5–10% of body weight, and maintaining the loss, in order to reduce the risk of developing chronic medical conditions [6]. Whilst a number of current interventions assist individuals to reduce 5–10% of their body weight, most people regain the weight once professional contact ends [7]. Therefore, new treatment interventions which assist with weight-loss maintenance are urgently needed.

Recent research has examined the role of executive function in individuals with obesity. Executive function refers to a range of higher-order cognitive processes that facilitate initiation, planning, inhibition, cognitive flexibility, working memory, self-regulation, sequencing, and the achievement of complex, goal-oriented behaviour [8]. Obesity has been linked to deficits in executive function. A review of 24 studies found highly consistent results, with 22 studies showing a negative association between obesity and executive function [9]. This finding remained consistent even after controlling for age, sex, education, socioeconomic status, smoking, and cardiovascular and metabolic markers. Obese individuals with and without binge-eating disorder (BED) have been shown to have similar cognitive deficits [10]. In combination, these findings support a link between obesity and deficits in executive functioning, irrespective of common psychological or medical comorbidities.

The exact mechanism through which obesity and cognitive function are linked remains unknown. Smith and colleagues [9] have argued that a bidirectional relationship between executive function and obesity may be present whereby obesity impairs executive function via biological mechanisms, such as glucose abnormalities or inflammatory markers, and deficits in executive function exacerbate weight gain by causing difficulties with the regulation of food intake, and an inability to plan ahead or inhibit responses or a tendency to act impulsively. Research supports the notion that executive functioning is an important predictor of healthy eating, breakfast consumption and the inhibition of alcohol consumption [11–13] which are all predictors of obesity. Targeting these deficits in the obese may potentially improve a person’s response to therapy. This line of enquiry has led to the development of a new form of treatment for weight disorders, namely Cognitive Remediation Therapy for Obesity (CRT-O) [9, 14].

CRT-O is a manualised, face-to-face treatment that aims to improve underlying executive function deficits. It consists of mental exercises aimed at improving cognitive strategies, thinking skills and information processing through practice [14]. CRT for Anorexia Nervosa (CRT-AN) has been shown to be effective at improving executive function and eating-disorder-related quality of life (post treatment) and reducing psychopathology (at 6-month follow-up) [15]. Unlike CRT-AN, CRT-O is intended to assist people to maintain weight loss and prevent weight gain by associating cognitive style to food intake and exercise behaviours.

Our recent randomised controlled trial (RCT) on CRT-O for obesity [16] provided evidence for the efficacy of CRT-O. Eighty obese individuals received three 90-min sessions of behavioural weight loss (BWL: a standard weight-loss treatment) and were then randomised to either eight sessions of individual face-to-face CRT-O or a no-treatment control condition. Results showed that those in the CRT-O group experienced a significant improvement in executive function and a significant decrease in weight compared to controls, both with large effect sizes, and that changes in executive function predicted changes in weight. Participants also had a significant reduction in binge eating in the CRT-O condition, compared to controls. This highlights that CRT-O can improve executive function and help individuals to manage their weight. The data from this trial suggests that CRT-O could enhance weight-loss outcomes, without targeting eating or exercise behaviour directly.

Our present RCT will endeavour to determine the effectiveness of eight individual sessions of CRT-O plus 12 group sessions of BWL compared to eight individual and 12 group sessions of BWL alone (standard care) in obese patients, in terms of reducing weight, binge eating, grazing, and improving executive function and quality of life. In addition, as high levels of inflammation have been proposed to contribute to executive function deficits in obese individuals, inflammatory markers will be assessed to test this hypothesis [17]. We hypothesise that those who receive CRT-O plus BWL will show greater weight loss, improved executive functioning and quality of life, and reduced binge eating/grazing compared to individuals in the BWL alone condition at post-treatment and 1-year follow-ups.

